#### Conventional ESD procedure

2.7.2

After marking around the lesion with an electrosurgical knife and submucosal injection, submucosal dissection will be performed without any traction in principle, and the lesion will be removed.

#### EndoTrac ESD procedure

2.7.3

After marking around the lesion with an electrosurgical knife and submucosal injection, circumferential incisions will be made and the submucosa will be trimmed at the edge of the incision. The endoscope will be withdrawn to set up the EndoTrac procedure. A reusable delivery/development catheter with a hemoclip will be inserted through the accessory channel of the endoscope. After the loaded clip is opened, the nylon thread loop of the EndoTrac will be hooked to the clip, the stopper of the hand control unit will be removed, t-shaped handle will be pulled to shrink the loop, and the EndoTrac will be fixed to the clip. The operator will place the endoscope and EndoTrac at the gastric lesion, and the clip will be fired with the EndoTrac to the edge of the lesion for traction. The anchoring sites of the clip will depend on whether the scope position is straight or retroflex. During submucosal dissection, the lesion can be pulled or pushed freely with the hand control unit for appropriate view and traction. Dissection will be continued and the lesion removed.

### Primary endpoint

2.8

The primary endpoint will be ESD procedure time, defined as the time from the start of submucosal injection to the end of tumor removal. If an expert replaces a trainee during the procedure, the time required by the expert will be included in the procedure time for the trainee.

### Secondary endpoints

2.9

Secondary endpoints will include ESD procedure time according to the proficiency of the operator (trainee or expert), tumor size (≤20 mm or >20 mm), tumor location, the presence of an ulcer (UL) (positive or negative), and institution (high volume or low volume center).

Operators who have performed ≤40 ESD procedures previously will be considered trainees, and those who have performed >40 ESD procedures will be considered experts.^[2,7,8,20–22]^ Tumor location will be defined as the affected portion of the stomach (upper, middle, or lower third) or the surface of the stomach (lesser curvature, greater curvature, anterior wall, or posterior wall), according to the Japanese classification of gastric carcinoma.^[23]^ Findings consistent with an UL will be evaluated pathologically, with the presence of an UL or UL scar defined as UL-positive. Institutions performing ≤120 and >120 gastric ESDs per year will be classified as low and high volume centers, respectively.

Also evaluated will be the time for equipping the EndoTrac, defined as the time from insertion of the reusable delivery/development catheter with a hemoclip through the accessory channel of the endoscope to the time when the clip with the EndoTrac is attached to the lesion for traction, and the time from starting traction with the EndoTrac to complete resection. Other secondary outcomes will include the clip slip-off rate during EndoTrac ESD, defined as the number of times a clip slips off the lesion before the end of the procedure; the number of EndoTracs used per patient; and the conversion rate between conventional and EndoTrac ESD.

The rate of damage to the specimen will also be evaluated, and defined in the absence of the EndoTrac as damage within the specimen area delimited by the marked points, or traction-related damage caused by movement of the EndoTrac or the related endoscope within the specimen area delimited by the marked points.

Histologic outcomes will include en bloc, R0, and curative resection rates, tumor depth, sizes of the specimens and tumors, histologic type, ulcerative findings, and margin involvement. En bloc resection will be defined as removal of the entire tumor as a single piece; R0 resection as en bloc resection with lateral and vertical margins free of tumor cells; and curative resection as pathologically eCura A or eCura B, as defined by the Japanese gastric cancer treatment guidelines 2018.^[18]^

AEs will include post-ESD bleeding, clinical symptoms, need for emergency endoscopy, perforation, and pneumonia. Post-ESD bleeding will be defined as hemorrhage with clinical symptoms, confirmed by emergency endoscopy, from the time of the completion of ESD until the end of the protocol. Clinical symptoms will include hematemesis, melena or a >2 g/dL reduction in hemoglobin concentration since the patient's most recent laboratory test. An emergency endoscopy will be defined as an endoscopy performed on a patient who experienced clinical symptoms with suspicion of post-ESD bleeding. Patients who underwent hemostasis for subclinical bleeding without any suspicion of post-ESD bleeding during second look endoscopy will not be regarded as experiencing post-ESD bleeding.^[24]^ Perforation will be defined as mesenteric fat or the intra-abdominal space observed during the procedure or free air found on radiography or computed tomography. Pneumonia after ESD will be defined as clinical findings suggesting pneumonia and radiographic or computed tomography evidence of pneumonia.

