**Methods/design::**

This multicenter, randomized control trial will enroll 150 patients at 2 hospitals in Japan undergoing EndoTrac or conventional ESD for gastric epithelial neoplasia. Patients with a single gastric epithelial neoplasm who meet the inclusion and exclusion criteria will be randomized to EndoTrac or conventional ESD. Patients will be randomized by a computer-generated random sequence with stratification by operator experience, tumor size, tumor location, and institution. The primary endpoint will be ESD procedure time, defined as the time from the start of the submucosal injection to the completion of resection. Other outcomes will include the rates of adverse events and pathological curability

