### Study aims and design

2.2

This prospective RCT will enroll patients with gastric epithelial neoplasia undergoing ESD at 2 hospitals in Japan. The trial is designed to determine whether EndoTrac ESD provides better efficacy and safety than conventional ESD in patients with gastric epithelial neoplasia. The primary endpoint will be ESD procedure time.

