### Statistical analysis

3.2

The primary endpoint is procedure time, defined as the time from the start of local injection into the submucosal layer to the end of detachment. The multiple regression analysis will be performed to estimate the treatment effect between groups adjusted with the stratified factors (i.e., operator proficiency, tumor size, institution and lesion location).

The secondary endpoint includes the factors associated with ESD procedure time which consist of operator proficiency (trainee vs expert), tumor size (≤20 mm vs ≥20 mm), lesion location, findings associated with UL (positive vs negative), and institution (high volume center vs low volume center); EndoTrac equipping time; time from starting traction with EndoTrac to complete resection; clip slip-off rate during EndoTrac and number of EndoTrac used; conversion rate; rate of specimen damage; histologic findings; and AE. The continuous outcomes will be summarized into the mean and standard error. When these outcomes have non-normal distribution, will be used the median and interquartile range as summary statistics. The categorical values will be summarized into frequency (proportion).

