EndoTrac has advantages over clip-with-line traction methods. The EndoTrac can not only control the degree of strength but the direction of traction. Use of the EndoTrac enables coordination of an appropriate direction by pulling or pushing the sheath to achieve the desired traction. The clip-with-line method can pull but not push the lesion, with this 1-way traction resulting in inappropriate or excessive traction, preventing the operator from recognizing the appropriate submucosal layer for dissection.

To the best of our knowledge, the study described herein will be the first prospective randomized control study to compare the efficacy and safety of EndoTrac ESD with that of conventional ESD for gastric tumors. Use of a randomized controlled design can reduce biases associated with retrospective studies, such as patient selection, operator selection, small sample size, and the unconscious choice to use EndoTrac.

Factors associated with technical difficulties and long procedure times for gastric ESD include larger lesion sizes, lesions located in the middle and upper two-thirds of the stomach, lesions located in the greater curvature, presence of ulceration, and an operating physician who has performed <40 of these procedures.^[2,7,8,20–22]^ To determine whether these factors are also associated with greater difficulties in patients undergoing EndoTrac ESD, we plan to randomize patients to undergo EndoTrac or conventional ESD by dynamic balancing using the minimization method, and with stratification by operator experience (trainee vs expert), tumor size (≤20 mm vs >20 mm), tumor location (upper/middle thirds vs lower third), and institution (high vs low volume center). The major limitation of this study is that the operator is not blinded to treatment group allocation.

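### With only two hospitals, procedure time by high- versus low-volume center is a contrast between two particular hospitals and should be labelled and read as that

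*Protocol article*

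**What the plan says.** Section 2.2 states that the trial enrolls patients "undergoing ESD at 2 hospitals in Japan", and the Abstract agrees: it "will enroll 150 patients at 2 hospitals in Japan".

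Section 2.9 lists procedure time by several factors as secondary endpoints, one of them "institution (high volume or low volume center". It then gives the classification: "Institutions performing ≤120 and >120 gastric ESDs per year will be classified as low and high volume centers, respectively".

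Section 3.2 repeats the factor as "institution (high volume center vs low volume center" in its list of factors associated with procedure time. For the primary endpoint, the same section adjusts a multiple regression for the stratification factors, institution among them.

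Sections 2.3 and 2.6 name the minimization factor simply as institution. The Discussion (section 5) writes the same factor as "institution (high vs low volume center".

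**The concern.** The classification works at hospital level, and there are two hospitals. With one in each class, the volume variable and the hospital variable divide the patients identically. Whatever else differs between the two sites (individual operators, referral pattern, equipment) comes with the label. Section 2.7 fixes the knife but leaves endoscope, needle, hemostatic forceps and hood free, so equipment may well differ by site.

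What is at stake is the meaning of one secondary result. If the plan is followed as worded, a difference in procedure time between two named hospitals, or a difference in the EndoTrac effect between them, would be published as a finding about center volume.

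**Working it through.** The article gives no figure for the volume comparison, so none has to be reproduced. The check concerns what the design can identify.

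**Step 1. Inputs.** Two hospitals (Abstract; section 2.2). One two-level factor defined per hospital, with the cut at 120 gastric ESDs per year (section 2.9). The article does not give the hospitals' annual numbers. The Discussion's wording indicates one hospital per class, and I take that as given.

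**Step 2. Degrees of freedom.** A statement about volume classes needs variation between hospitals of the same class as its yardstick. Degrees of freedom for that variation = hospitals − classes = 2 − 2 = 0. Patient numbers do not enter the formula.

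**Step 3. What can be estimated.** The difference in mean procedure time between the two hospitals, overall or within each arm, has an ordinary patient-level standard error. So has the difference between hospitals in treatment effect.

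**Step 4. Why that standard error does not serve a volume statement.** Write σ for the patient-level SD and τ for the SD between hospitals of the same class. The variance of the observed contrast, taken as an estimate of a class difference, is

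σ²(1/n₁ + 1/n₂) + 2τ².

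More patients shrink the first term only, and the trial cannot estimate τ.

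For scale, take σ from section 3.1: √((79.5² + 71.6²)/2) = √5723.4 = 75.65 minutes. This SD is consistent with the stated sample size:
- With a difference of 118.2 − 82.2 = 36.0 minutes, the normal approximation gives 2 × (1.960 + 0.842)² × 5723.4 / 36.0² ≈ 69.3, so 70 per arm and 140 in all.
- The t-based calculation gives the stated 142, and 142/0.95 rounds up to the planned 150.

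Assume 75 patients per hospital (the article gives no split). The first term is then 5723.4 × 2/75 = 152.6, a patient-level standard error of √152.6 = 12.4 minutes. The documents give no τ, so the values below are assumptions:

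| Assumed τ (min) | 152.6 + 2τ² | Standard error for a class difference (min) |
|---|---|---|
| 0 | 152.6 | 12.4 |
| 5 | 202.6 | 14.2 |
| 10 | 352.6 | 18.8 |
| 15 | 602.6 | 24.5 |
| 20 | 952.6 | 30.9 |

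The patient-level figure is right for a volume statement only if hospitals of the same class do not differ at all (τ = 0). The trial cannot check that.

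**The case against.** The strongest defence is that the label is only a convenient name for the two sites. With one hospital per class, institution and volume are the same partition, so the Discussion does not contradict sections 2.3 and 2.6. This stands, and it is the reason to use the plain label: the partition is harmless, while the name suggests a cause.

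A second defence is that operator experience, tumor size and location are minimization factors and covariates, so part of the case mix is accounted for. This stands in part. Minimization balances the arms, not the hospitals, and adjustment for three measured factors does not remove the remaining site differences.

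A third is that no test of volume is written down. After the list of secondary endpoints, section 3.2 gives summary statistics only. This also stands, so no error rate for such a test can be charged to the plan.

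A reader might infer more than the article supports:

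- *That it plans a claim about adoption in low-volume centers.* It does not. The Abstract speaks of wider adoption through reduced technical difficulty and does not mention center volume.
- *That the Discussion sets out to learn whether volume makes EndoTrac ESD harder.* The difficulty factors listed there are lesion size, location, greater curvature, ulceration and operator experience. Center volume is not among them.
- *That nothing can be estimated, or that the model is rank-deficient.* The hospital contrast is estimable. Redundancy would arise only if hospital and volume were entered together, and section 3.2 names institution once.
- *That both hospitals may share a class, or that one may cross 120 during enrolment.* No annual numbers are given, and the Discussion's wording points to one hospital per class.

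**Conclusion.** The concern holds as a point of labelling and interpretation. The comparison in sections 2.9 and 3.2 is a comparison of two particular hospitals, with 0 degrees of freedom to support a statement about volume classes at any sample size. This rests on the stated number of hospitals and on one hospital falling in each class. It does not depend on the assumed values of τ, which only give a sense of scale.

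The effect on the trial is small. Adjusting for institution as a two-level factor is valid, so the primary analysis stands, as do the sample size and the randomization. What changes is the conclusion that one secondary endpoint may carry.

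**What to change.** In sections 2.9, 3.2 and 5, name the factor institution (hospital A versus hospital B). Report procedure time by hospital, overall and by arm, as a descriptive result, and draw no inference about center volume. Each hospital's annual number of gastric ESDs may stay as a description of the site.

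Keep institution as minimization factor and as covariate in the primary model. For the experience question, rely on the planned trainee/expert comparison (≤40 versus >40 previous ESDs, section 2.9). That factor belongs to the operator and can vary within a hospital.

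The cost is a change of wording and the loss of a comparison labelled as volume. No data collection, sample size or primary analysis changes.

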### Randomization and blinding

2.6

Patients will be randomly assigned 1:1 to undergo conventional ESD or EndoTrac ESD. Random assignment will be centrally controlled by the Internet Data and Information Center for Medical Research cloud version (INDICE Cloud), supported by University Hospital Medial Information Network. Randomization will be performed via dynamic balancing using the minimization method, with stratification by operator experience (trainee or expert), tumor size (≤20 mm or >20 mm), tumor location (upper/middle thirds or lower third of the stomach), and institution. Neither patients nor physicians will be blinded to patient allocation.

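### Specimen damage is defined by whether EndoTrac is present; read literally, non-traction damage goes uncounted in EndoTrac specimens

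*Protocol article*

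**What the plan says.** Section 2.9 (Secondary endpoints) announces the endpoint: "The rate of damage to the specimen will also be evaluated". One sentence then defines it in two parts joined by a single conjunction: "defined in the absence of the EndoTrac as damage within the specimen area delimited by the marked points, or traction-related damage caused by movement", with the device or its endoscope named as what moves.

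- First part, up to the conjunction: damage inside the marks when the device is absent. No cause is required.
- Second part, in full: "traction-related damage caused by movement of the EndoTrac or the related endoscope within the specimen area delimited by the marked points". The area is the same, but the damage must be traction-related and due to movement of the device or its endoscope.

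Section 3.2 (Statistical analysis) repeats the endpoint by name only, in the list "conversion rate; rate of specimen damage; histologic findings; and AE". It gives no common definition, and for categorical outcomes it names frequency and proportion without a between-group test. Section 2.2 sets a comparative aim, to "determine whether EndoTrac ESD provides better efficacy and safety than conventional ESD". Section 2.6 states: "Neither patients nor physicians will be blinded to patient allocation".

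**The concern.** A rate can be compared between two groups only if the same event is counted in both. Here the broad part of the definition depends on the device being absent, and the narrow part can be met only when the device is present.

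Under section 2.7 both arms use the same knife, may use hemostatic forceps, and may use a snare if required. Damage unrelated to traction can therefore occur in either arm. Under the literal rule it is an event in a conventional specimen and not in an EndoTrac specimen. Section 2.7.2 says conventional ESD is done without traction in principle, so no matching exclusion applies on that side.

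Specimen damage bears on the comparative efficacy and safety aim. If the case report form follows the sentence, non-traction damage in EndoTrac specimens may never be recorded, and no later analysis can restore it. Deciding that damage is traction-related is also a judgement, made in a trial where the physicians know the allocation.

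**Working it through.** **The plan's own figures.** The article gives no specimen damage rate and no split by cause, so there is no stated figure to reproduce for this endpoint. The only planned number used below is the arm size: 150 patients randomised 1:1 gives 150 / 2 = 75 per arm (sections 2.6 and 3.1).

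**Step 1: parse the sentence.** If the absence qualifier governed both parts, the second would be impossible, because an absent device cannot move. The qualifier must therefore attach to the first part. Taken literally, the rule is:

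| Kind of damage inside the marks | EndoTrac absent | EndoTrac used |
|---|---|---|
| Traction-related, from movement of the device or its endoscope | does not arise | counted |
| Any other cause (for example knife, coagulation, snare) | counted | not counted |

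**Step 2: effect on the difference.** Let q be the probability of non-traction damage, taken as equal in both arms, and t the probability of traction damage in EndoTrac specimens. Take the two as independent and ignore conversions.

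- Common definition: conventional q; EndoTrac q + t − qt; difference (EndoTrac minus conventional) t − qt.
- Literal definition: conventional q; EndoTrac t; difference t − q.
- Shift caused by the wording: (t − q) − (t − qt) = −q(1 − t), which is about −q when t is small.

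The shift favours EndoTrac for any q above zero. If q differs between arms, the q that matters is the one in EndoTrac specimens.

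**Step 3: size under assumed values.** Non-traction damage uncounted by the literal rule is about 75q specimens in the EndoTrac arm (exactly 75q(1 − t), because a specimen that also has traction damage is still counted):

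- q = 5%: 75 × 0.05 = 3.75, about 4
- q = 10%: 75 × 0.10 = 7.5, about 8
- q = 15%: 75 × 0.15 = 11.25, about 11

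The apparent difference also depends on t:

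| Assumed q | Assumed t | Difference, common definition | Difference, literal definition | Shift |
|---|---|---|---|---|
| 15% | 0% | 15 − 15 = 0 points | 0 − 15 = −15 points | −15 |
| 10% | 5% | 14.5 − 10 = +4.5 points | 5 − 10 = −5 points | −9.5 |
| 10% | 10% | 19 − 10 = +9 points | 10 − 10 = 0 points | −9 |
| 5% | 10% | 14.5 − 5 = +9.5 points | 10 − 5 = +5 points | −4.5 |

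The shift is always in the same direction, but it becomes an apparent EndoTrac advantage only when q exceeds t.

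**Step 4: a second way to see it.** Suppose total damage is truly p in both arms and a share s of EndoTrac damage is not traction-related. The literal rule then shows p against p(1 − s), a risk ratio of 1 − s where the true ratio is 1. With assumed p = 10% and s = 50%, that is 10% against 5%, or 7.5 against 3.75 expected specimens per 75.

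**Step 5: conversions.** Section 2.7 lets a patient in either arm convert to the other procedure once the procedure has run at least 60 minutes and continuing as assigned is deemed impossible. The definition turns on presence of the device, not on randomised arm. It does not say which part applies to a specimen dissected partly with EndoTrac and partly without.

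**The case against.** The best defence is that the sentence is loosely worded and means a union: damage not due to the EndoTrac, or damage due to traction, in every patient. The article never says that damage in EndoTrac specimens counts only if traction-related; that restriction follows from the absence qualifier. On the union reading both arms count all damage and the shift is zero. The reading is possible, and the full protocol behind the article is not shown. But the qualifier does not say this, and no other section repairs it. A true union would be simply any damage inside the marks, which is the wording recommended below.

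A second defence is that this is one item in a long secondary list, with only descriptive summaries named. En bloc, R0 and curative resection and margin involvement are collected separately, and their definitions do not mention the device. That stands and limits the importance of the point. It does not make a pair of proportions comparable when they count different events.

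Some stronger inferences should be resisted:

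- A reader might infer that traction damage itself is hidden. It is not: the second part of the definition counts it. It can only be offset in the between-arm difference, as in the third row of the table.
- A reader might infer that converted patients fit neither part. Since the split is by device use, they may fall under either or both; their classification is undefined.
- A reader might infer that an unblinded operator scores the damage. The article does not say who scores it.

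**Conclusion.** The point holds as a defect in a stated definition. On its literal reading, section 2.9 counts non-traction damage only where EndoTrac is absent. This moves the difference in EndoTrac's favour by about q, or exactly q(1 − t) under independence. The direction follows from the wording. The size cannot be determined from the article: the 5 to 15 point range, about 4 to 11 of 75 specimens, is an assumption about q and nothing more.

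It would be tempting to call this a spurious 5 to 15 point advantage for EndoTrac. The documents do not support that, because the apparent advantage equals q only if traction damage is near zero. Nor do they support saying that the definition differs strictly by randomised arm, or that the comparison is certainly biased, since a union may have been intended.

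The consequence is confined to one descriptive secondary endpoint. The primary endpoint, its regression and the sample size are unaffected. The correction is worth making because it is nearly free and the endpoint bears on the comparative aim, but the trial's main result does not depend on it.

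**What to change.** Replace the two-part sentence in section 2.9 with one cause-neutral definition for both arms: any damage inside the marked points, scored present or absent per specimen. Report it by randomised arm, which also settles how converted cases are handled. Record whether damage is judged traction-related as a descriptive sub-category that does not decide whether the event counts. Where feasible, have the pathology read that is already done score the item without knowledge of the arm.

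The cost is a one-sentence amendment, one case report form item and some re-coding. Enrolment began in June 2021, so specimens already scored would need re-coding from reports or photographs where these exist; any that cannot be re-coded should be reported as such. If a union was intended all along and forms were completed that way, the amendment only clarifies the text and no re-coding is needed.
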